#### Other assessments

2.6.3

Demographic and socioeconomic characteristics from clinical routine data include age, sex, marital status, level of education, professional qualifications and apprenticeships or studies.

Occupational data include weekly working hours, receipt or application for a pension, unemployment at the time of admission, and incapacity to work in the last 12 months before admission to rehabilitation.

Inpatient treatment data includes admission and discharge dates, discharge type, and ICD 10 diagnoses.

Recommendations for medical procedures and rehabilitation aftercare by the rehabilitation clinic are documented.

General feedback is assessed through a self-constructed item (‘What else would you like to tell us?’).

Adherence is assessed in different areas throughout *marena*. To analyze the use of the task organizer the number of completed tasks will be examined in relation to the number of tasks that became active in the participant's aftercare plan. Adherence is operationalized by the percentage of participants who completed at least the lower quartile of the provided tasks (in relation to the sample). Additionally, the number of sessions, completed weekly surveys, media playback, visits to the intervention areas, and individual pages will be analyzed. To operationalize adherence to *GSA-Online plus*, the number of completed writing-impulses will be assessed. Adherence will be operationalized by the percentage of participants who wrote at least the lower quartile of diary entries written in the sample.

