### Sample size

2.7

The sample size was determined a priori using SAS 9.4 software. A Power analysis based on a power of 0.80, two-sided testing, an alpha-rate of 5 %, and a randomization ratio of 3:1 was conducted. According to Bethge (2017), Odds Ratios of 3.49 (referring to Streibelt and Bethge, 2014) and 2.41 (in Bethge et al., 2011; overall in Streibelt and Bethge, 2014) were observed for work-related occupational rehabilitation programs versus medical rehabilitation with regard to work status 6 months after discharge from rehabilitation. We plan more conservative with an Odds Ratio of 2.0. According to Bethge (2011), a work status rate of 51 % in the CG could be assumed. These assumptions resulted in a total sample size of *N* = 360 required for 80 % power and a binary logistic regression model to analyze the primary endpoint. When considering a correlation of ρ = 0.4 with indicators of specific occupational problems (at least 3-months of incapacity to work before rehabilitation, unemployment at the time of application, and the socio-medical assessment of limited performance in the last occupational activity; see also Bethge, 2017), the sample size can be reduced by ρ2 = 16 % to *N* = 320, due to the reduction of total variance through the explained variance of the covariates. Based on an estimated dropout rate of 20 % at the follow-up assessments T1 (at the end of the *GSA-Online plus* intervention) and T2 (at the end of the *marena* intervention) we plan to randomize *N* = 400 patients.

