### Statistical analysis for primary and secondary outcomes

2.9

All data analyses will be performed after completion of data collection and on intention-to-treat basis. The significance level for all analyses will be defined as *p* = .05. If appropriate, results will be displayed by adjusted estimates from the analysis model, and their respective 95 % confidence intervals. Descriptive statistics will be used to describe demographics and baseline characteristics. To examine differences between IG and CG in the dichotomous primary outcome work status at 6 months (T2, primary endpoint) and 12 months (T4, secondary endpoint), a binary logistic regression model with fixed and random effects will be performed. In the logistic regression model the following parameters will be considered as fixed effects: treatment group (IG/CG), study site, operating system (android/iOS), at least 3-month incapacity for work before rehabilitation (yes/no), and unemployment at the time of admission to rehabilitation (yes/no). The social-medical risk index (SIBAR) as a continuous parameter will serve as a random effect. In addition, per protocol analyses will be performed to examine the impact of dropouts on study results. Dichotomous secondary outcomes will be analyzed accordingly. Continuous outcome measures will be analyzed with a covariance model for repeated measures. Compound symmetry will be assumed. Additionally, per protocol analyses (based on data of those participants who completed at least the lower quartile of tasks provided in *marena* in relation to the sample and participants who wrote at least the lower quartile of diary entries written in the *GSA-Online plus* sample) will be performed to examine the impact of dropouts on study results. Furthermore, other possible influencing factors (e.g., IG subgroup 1 and IG subgroup 2, received aftercare vs. not received aftercare) will be examined in an exploratory way. The results will also be displayed by rehabilitation center to explore whether obvious differences in effect sizes by rehabilitation center are apparent.

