### Limitations

3.2

First, we emphasize that there is no randomization between the two IG subgroups, as recommendations are made by the clinic staff. Therefore, selection bias may limit the generalizability of the results. To reduce bias, standardized training and information materials are provided to ensure that the selection of participants is as objective as possible.

Second, due to the nature of the intervention, study participants will not be blinded. Participants in the CG, who will not have access to the full version of *marena*, will be aware when reading the consent form and attending the group presentation, fellow patients will have access to a more favorable version of the intervention. To mitigate this potential disincentive, we decided to use an optimized CG.

Third, it should also be noted that content in *marena* supports participants during a graded return to work, where participants remain on formal sick leave, and thus provides content that actively leads to inability to work. This may have a negative impact on the primary outcome work status. To reduce the risk of confounding of the criterion, we will not include work incapacity due to graded return to work in the outcome. Furthermore, including the duration of work incapacity in the screening instrument as well as the primary outcome may also confound the results.

Furthermore, a high dropout rate is to be expected, as internet-based interventions are typically subject to low adherence, especially in the CG. Therefore, multiple features of *marena* are designed to encourage compliance and questionnaire response, such as task reminders and questionnaires that are set to be active for a period of time and become mandatory close to the measurement points.

Last, the different functionality of *marena* on the Android (push notifications and e-mail) and iOS (e-mail only) operating systems may contribute to differences in user compliance. To control for this, the operating system used is included in the analysis as a control variable.

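### The per-protocol and adherence rules cut at the sample's own lower quartile, cannot be applied to the control group, and do not select on observed outcomes, so they cannot serve as the check on dropout

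*Protocol article*

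**What the plan says.** Section 2.9 makes intention-to-treat the basis of all analyses and adds per-protocol analyses in two places. The first mention follows the logistic model for work status: "per protocol analyses will be performed to examine the impact of dropouts on study results". It defines no set. The second follows the model for continuous outcomes, repeats the purpose and gives the rule: "per protocol analyses (based on data of those participants who completed at least the lower quartile of tasks provided in" *marena*, relative to the sample, together with those at or above the lower quartile of diary entries in the *GSA-Online plus* sample.

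Section 2.6.3 uses the same cut-offs to define the adherence rate. For *marena* it is the percentage of participants at or above the lower quartile of provided tasks, again relative to the sample. For the writing intervention: "Adherence will be operationalized by the percentage of participants who wrote at least the lower quartile of diary entries written in the sample".

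Section 2.5 gives the control group (CG) questionnaires and voluntary weekly surveys only. Neither section states a per-protocol criterion for the CG. Section 3.2 warns that "a high dropout rate is to be expected, as internet-based interventions are typically subject to low adherence, especially in the CG".

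**The concern.** Three features of the rule work against its purpose.

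- **The cut-off moves with the data.** A threshold at the sample's own lower quartile is passed by about three quarters of users or more, however much or little they used the program. It is also known only once usage has been seen.
- **The criteria exist in one arm only.** Tasks and diary entries are intervention-group (IG) activities. A set defined by them cannot be formed in the same way in the CG.
- **The rule selects on usage, yet it is presented as a check on dropout.** For the trial's estimate, the dropout that matters is missing work status at 6 months (T2) and 12 months (T4).

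At stake are the reported adherence rate, how any per-protocol effect will be read, and whether readers will believe that loss to follow-up has been examined when it has not been examined by this analysis.

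**Working it through.** **Inputs from Section 2.7.** The design has "a power of 0.80, two-sided testing, an alpha-rate of 5 %, and a randomization ratio of 3:1". On the effect: "We plan more conservative with an Odds Ratio of 2.0". On the CG: "a work status rate of 51 % in the CG could be assumed". Dropout is put at 20% ("Based on an estimated dropout rate of 20 % at the follow-up assessments T1" and T2).

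**The plan's own figure.** The IG odds are 2.0 × 0.51/0.49 = 2.082, so the IG rate is 2.082/3.082 = 67.5%. A pooled two-proportion calculation at 3:1 gives 90 + 270 = 360, as stated. The last step also reproduces: 320/(1 - 0.20) = 400. The plan gives no figure for the per-protocol set or the expected adherence rate, so the consequences of the rule have to be worked out.

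**Step 1: adherence rate under a sample-quartile cut-off.** The share with usage at or above the sample's 25th percentile was simulated for assumed usage patterns.

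| Assumed usage | Lower quartile | Counted as adherent |
|---|---|---|
| Tasks, median completion 82% | 73% | 75.0% |
| Tasks, median completion 50% | 33% | 75.0% |
| Tasks, median completion 7% | 3% | 75.0% |
| Diary entries, binomial (12, 0.7) | 7 | 88% |
| Diary entries, 30% of users write none | 0 | 100% |

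Ties can only raise the share. Once the quartile is zero, non-users count as adherent.

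**Step 2: the contrast between arms.** There are two ways to treat the CG.

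- Read literally, CG patients complete no tasks and write no entries, so none qualifies and there is nothing to compare.
- If the CG is kept whole, the lowest quarter of the IG by usage is removed and nobody is removed from the CG.

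For the second reading, take no treatment effect and 51% in both arms. If the removed quarter has success rate p_n, the retained IG rate is p_a = (0.51 - 0.25 × p_n)/0.75, and the odds ratio is [p_a/(1 - p_a)]/(0.51/0.49). Values of p_n come from a bivariate normal model with an assumed correlation r between usage and the tendency to a positive work status. The documents give no such correlation.

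| r (assumed) | p_n | p_a | Odds ratio |
|---|---|---|---|
| -0.2 | 61.2% | 47.6% | 0.87 |
| 0 | 51.0% | 51.0% | 1.00 |
| 0.2 | 40.8% | 54.4% | 1.15 |
| 0.3 | 35.6% | 56.1% | 1.23 |
| 0.4 | 30.3% | 57.9% | 1.32 |

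The false-positive rate can be put on the plan's own numbers: 320 analysed at 3:1 is 80 CG and 240 IG, and 0.75 × 240 = 180 IG are retained. For p_n = 40%, p_a = (0.51 - 0.10)/0.75 = 54.7%. The pooled rate is (80 × 0.51 + 180 × 0.547)/260 = 0.535, the null standard error is 0.0670 and the alternative standard error is 0.0671. A nominal 5% two-sided test then rejects with probability Φ((0.0367 - 1.96 × 0.0670)/0.0671) + Φ((-0.0367 - 1.96 × 0.0670)/0.0671) = 0.079 + 0.006 = 8.5%. The same calculation gives 6.0% for p_n = 45% and 18.3% for p_n = 30%.

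**Step 3: rule against stated purpose.** The rule can be set against the four kinds of patient that matter for loss to follow-up.

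| Patient | Effect of the rule |
|---|---|
| IG, adequate use, T2 missing | kept, outcome still missing |
| IG, low use, T2 observed | removed although the outcome is known |
| IG, low use, T2 missing | removed, outcome still unknown |
| CG, T2 missing | not addressed |

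No row tells the analyst what the missing outcomes might do to the estimate. The last row is the one that Section 3.2 singles out.

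**The case against.** Several counter-arguments have force.

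- **Supplementary role.** Intention-to-treat is the stated basis and the per-protocol analyses are additional. This stands in full: the primary estimate does not depend on the rule.
- **Scope of the rule.** The quartile rule is spelled out only at the second mention, after the continuous outcomes. Applying it to work status is the natural reading, but it is not stated. The one-arm filter is likewise an inference, though the only alternative leaves no comparison.
- **Wording for *marena*.** The phrase could mean 25% of the tasks provided, which is a fixed threshold. The reference to the sample and the parallel diary wording point the other way, and that reading would repair only the first defect, for *marena* only.
- **Other usage data.** Section 2.6.3 also reports sessions, surveys, media playback and page visits, and already relates completed to activated tasks. The trial will therefore describe use, but its headline adherence percentage will not.
- **Two senses of dropout.** A usage-based set has some bearing on dropout from the intervention, and low use probably goes with non-response because the surveys run inside *marena* (Section 2.8). Neither helps with CG loss to follow-up.

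A reader might infer that the per-protocol effect is biased in favour of *marena*. The documents do not establish this. Tasks respond to reported setbacks and benefit applications (Section 2.4.1), so patients who return to work smoothly may use the app less, which would reverse the bias.

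A reader might also infer that missing outcomes distort the primary result, or that the plan needs multiple imputation in the primary analysis. The article does not state a complete-case analysis, gives no split of loss by arm, and may leave missing-data methods to an analysis plan that is not shown. An invented split does not settle it. With 40% loss in the CG, 13.3% in the IG and dropouts 20 points less likely to be working, complete-case rates rise by 0.40 × 20 = 8.0 points in the CG and 0.133 × 20 = 2.7 in the IG. That 5.3-point shift works against *marena*.

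**Conclusion.** The rule is wrong as written, in three limited respects.

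1. **Adherence.** The sample-quartile definition makes at least about 75% of users adherent by construction, and up to 100% with ties at zero. This is explicit for diary entries and the more natural reading for *marena* tasks.
2. **Contrast.** The per-protocol set yields either no IG-CG comparison or one that is biased unless usage is unrelated to prognosis. Under no effect, the odds ratio runs from 0.87 to 1.32 for correlations of -0.2 to 0.4. That range rests on assumed correlations and on keeping the CG whole. Neither the size nor the direction of the bias is known.
3. **Purpose.** The set cannot show the impact of loss to follow-up, because it does not select on whether work status was observed and does nothing about the CG.

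The fault lies in what the article fixes, not in its silence on imputation. The primary conclusion is not in question. What is affected is the adherence result and the only dropout check that the article names.

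**What to change.** - **Adherence and per-protocol threshold.** Replace the sample quartile by a fixed threshold set before usage data are seen: a stated share of the patient's own activated *marena* tasks and of the 12 weekly writing prompts.
- **Contrast.** Do not present the filtered IG against the unfiltered CG as a treatment effect. Label it descriptive, or replace it with an estimate that respects randomisation, such as a complier-average estimate. State the caveat that patients below the threshold still have access to *marena* and may benefit, which strains the exclusion restriction.
- **Dropout.** Delete the statement, in both places, that per-protocol analysis examines the impact of dropouts. Examine it with a sensitivity analysis of missing T2 and T4 work status by arm, for example counting missing as not positive, and a delta-adjusted analysis with the shift varied separately in each arm.

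The cost is revised wording and modest extra programming, with no new data.

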## Discussion

3

This RCT examines the efficacy of the newly developed internet- and mobile-based aftercare intervention *marena* concerning work status as the primary outcome, the success on work-related measures (graded return to work and benefits for participation in working life), current work ability, as well as psychosocial well-being as secondary outcomes. We will also examine aspects of acceptability, such as intervention satisfaction and adherence, to improve further development of the intervention. Rehabilitants with access to *marena* are compared to an optimized CG with limited access to the intervention. If the rehabilitation clinic staff identifies a need for more intensive and specific support in addition to *marena*, participants of the IG are given access to the web-based guided intervention, *GSA-Online plus.*

The *marena* intervention is designed as a low threshold application intended to support return to work following inpatient medical rehabilitation. To ensure that participants receive relevant information depending on how and when they return to their workplace, and which supporting measures are available, adaptable content and various components customized to the participants' input are provided. Content tailoring allows participants to make choices and report events in real time, which in turn, triggers different content based on preference or need. Results will contribute to the limited evidence on internet-based interventions focused on return to work in occupational health (Johnsen et al., 2021).

### Strengths

3.1

First, the intensive development phase for *marena* with expert consultation and feedback loops, as well as a pilot phase with patients to ensure the content is tailored to the target group and the intervention is user-friendly. This could also have a positive impact on adherence and on subsequent implementation in the healthcare system.

Second, the intervention aims to facilitate the transfer of customary strategies and aftercare goals into daily life, with content closely linked to inpatient and occupational rehabilitation. To accomplish this, specific aftercare plans are assigned, that contain sequences of tasks to be performed by the rehabilitants. If applicable to the participants, these plans include tasks to fulfill their legal obligations (e.g., sending a form to the pension insurance agency within the framework of a graded return to work). The aftercare plans are developed in a declarative way, allowing the activation and due dates of all tasks to be automatically and dynamically adapted to the development of the participants' status, thus providing unsupervised personalization of the participants' plans. By providing structure and guidance through additional information and encouragement, *marena* supports the implementation of action plans from inpatient rehabilitation into daily life, motivates participants to pursue their aftercare goals, and aims to achieve a sustainable anchoring of the successes of rehabilitation in subsequent work and everyday life.

Third, the stepped-care model with different levels of guidance ensures that the individual need for support is met. Internet-based aftercare provides the opportunity to reach patients independently of time and place. While guided approaches have shown to be most effective, they are also tied to greater intervention cost (Baumeister et al., 2014). Thus, investigating the efficacy and acceptability of an unguided aftercare intervention is particularly valuable.

Finally, we will be able to enroll a variety of patients in the target population of this study by recruiting across indications, in four different states, and in clinics with different health care providers (two German Pension insurance clinics, two private clinic operators). Participants will not be compensated for their participation. This real-world setting, reflecting the conditions of health care services, will add considerable validity to future findings and will provide very valuable information on the generalizability of study results as well as the long-term implementation and dissemination of both interventions.

### Limitations

3.2

First, we emphasize that there is no randomization between the two IG subgroups, as recommendations are made by the clinic staff. Therefore, selection bias may limit the generalizability of the results. To reduce bias, standardized training and information materials are provided to ensure that the selection of participants is as objective as possible.

Second, due to the nature of the intervention, study participants will not be blinded. Participants in the CG, who will not have access to the full version of *marena*, will be aware when reading the consent form and attending the group presentation, fellow patients will have access to a more favorable version of the intervention. To mitigate this potential disincentive, we decided to use an optimized CG.

Third, it should also be noted that content in *marena* supports participants during a graded return to work, where participants remain on formal sick leave, and thus provides content that actively leads to inability to work. This may have a negative impact on the primary outcome work status. To reduce the risk of confounding of the criterion, we will not include work incapacity due to graded return to work in the outcome. Furthermore, including the duration of work incapacity in the screening instrument as well as the primary outcome may also confound the results.

Furthermore, a high dropout rate is to be expected, as internet-based interventions are typically subject to low adherence, especially in the CG. Therefore, multiple features of *marena* are designed to encourage compliance and questionnaire response, such as task reminders and questionnaires that are set to be active for a period of time and become mandatory close to the measurement points.

Last, the different functionality of *marena* on the Android (push notifications and e-mail) and iOS (e-mail only) operating systems may contribute to differences in user compliance. To control for this, the operating system used is included in the analysis as a control variable.

### Conclusion

3.3

Patients returning to work following a medical rehabilitation face a diversity of challenges. Providing tangible and practicable advice regarding the pursuit of aftercare goals, aftercare programs/measures and benefits. If it proves to be effective, *marena* offers a highly adaptive, low-threshold approach to improve return to work in rehabilitation patients.

